## Results

Primary outcome

The primary outcomes of this study will be determined by the HAMA [18] scores and electroencephalogram (EEG) results. The HAMA scale consists of 14 items, which will be evaluated by professional psychiatrists before and after the treatment. The total HAMA score can range from 0 to 56, with anxiety levels classified as follows: possible anxiety for scores between 7 and 14, definite anxiety for scores between 14 and 21, moderate anxiety for scores between 21 and 29, and severe anxiety for scores greater than 29.

For the EEG, participants will be seated in a quiet environment, with their eyes closed, while maintaining an alert state. Scalp electrodes will be placed according to the international 10-20 system, using 17 disc electrodes with earlobes serving as reference electrodes. The EEG will record both bipolar and reference leads, with standard evoked tests (including hyperventilation, rhythmic photic stimulation, and eye-opening/closing tests) conducted during monitoring. The time constant will be set at 0.3 ms, the high-frequency filter will be set at 70 Hz, the standard voltage will be set at 10 mV/mm, and the recording time will be between 15 and 20 minutes.

Other outcome measures

Other outcome measures in this study include symptom signs, scores on the Hamilton Depression Rating Scale (HAMD), scores on the Symptom Checklist-90 (SCL-90), and results from monitoring the gut microbiota.

Hamilton Depression Rating Scale

This scale is used to assess the severity of depression in patients and consists of 17 items. Depression severity is classified based on HAMD scores as follows: a score of less than 7 suggests no depression; a score between 7 and 16 suggests possible depression; a score of 17 or greater indicates definite depression.

Symptom Checklist-90

This scale is used to evaluate patients' self-perceived symptoms during treatment. Each question is rated on a scale from 1 (none) to 5 (severe), with higher scores indicating more severe adverse symptoms.

Gut Microbiota Monitoring

Stool samples will be collected from randomly selected patients in the treatment and control groups before and after eight weeks of treatment. Samples will be collected in the morning, on an empty stomach, using a sterile spoon to obtain 3-5 g of fresh stool. These samples will be immediately placed in standardized sterile containers and stored at -80°C for subsequent analysis [19].

Safety assessments

All participants will undergo physical examinations and vital signs testing. Any adverse events will be documented in detail, and participants will receive appropriate treatment immediately. Most adverse events related to abdominal massage are mild, such as abdominal soreness, which typically resolves with rest. Severe adverse events will be promptly reported to the Ethics Committee of the First Teaching Hospital of Tianjin University of Traditional Chinese Medicine. Participants will decide whether to continue in the trial if adverse events occur.

Quality control, data management, and monitoring

Before the commencement of the trial, a clinical research manual will be prepared, and all researchers will undergo professional training to ensure their familiarity with the clinical research protocol and consistency in efficacy evaluations. Standard procedures for Tui Na operations will be established to ensure accuracy, and Tui Na practitioners will be periodically supervised.

All original patient data will be retained in case report forms, which will be stored in a secure, restricted environment. A researcher, who will not be privy to group assignments, will enter the data into a pre-designed, password-protected electronic database. Access to this database will be granted only to designated members of the research team.

To ensure privacy and confidentiality, all research documents will be stored in a locked cabinet located in a secured office in Chengdu. The Ethics Committee of the First Teaching Hospital of Tianjin University of Traditional Chinese Medicine may inspect research records and monitor the trial process to ensure adherence to ethical standards.

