## Introduction

Generalized anxiety disorder (GAD) is a mental health condition primarily typified by excessive anxiety, frequently accompanied by symptoms of autonomic nervous system dysfunction [1]. The global lifetime prevalence of GAD is estimated at 3.7% [2]. In China, anxiety disorders' prevalence stands at 5.0%, with a lifetime prevalence reaching up to 7.6%, making it one of the most common mental health conditions [3]. GAD not only undermines the physical and mental health of the affected individuals but also leads to significant social and occupational dysfunction, posing a severe impact on societal and global health [4]. It is the most prevalent type of anxiety disorder [5], with symptoms primarily manifesting as tension, worry, fear, and autonomic dysfunction [6].

At present, the first-line treatment for GAD consists of pharmacotherapy, including benzodiazepine anxiolytics, receptor blockers, and selective serotonin reuptake inhibitors (SSRIs), among others [7]. However, the long-term use of these medications can result in dependence, addiction, an increased incidence of adverse drug reactions, and potential drug resistance, thereby diminishing treatment effectiveness [8]. Moreover, some patients may find the side effects of these medications intolerable and may opt to discontinue treatment. Consequently, there is a pressing need in clinical practice for a safe, effective, and easily applicable treatment method for GAD.

In recent years, the use of Traditional Chinese medicine (TCM) therapies in GAD management has been gaining traction. Particularly, TCM massage, and more specifically abdominal massage, is highly favored by patients due to its capacity to regulate internal organs, promote qi circulation, and balance yin and yang, all while being safe and comfortable [9,10]. Thus, understanding the mechanisms of abdominal massage and other unique TCM therapies has emerged as a significant area of academic interest and a crucial factor in advancing the application and development of TCM.

Objectives

This study aims to evaluate the therapeutic efficacy of abdominal massage in conjunction with escitalopram for the treatment of GAD. By correlating EEG metrics with anxiety assessment scales, a quantitative relationship between symptom scores and objective examination measures is aimed to be established. This will provide auxiliary diagnostic criteria and objective metrics for evaluating clinical efficacy in GAD.

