## Materials and methods

Study design and setting

This study will be conducted as a parallel-designed, prospective, assessor-blinded, single-center randomized controlled trial. The timeline of this protocol study is from August 2024 to May 2025. This study will take place at the Department of Tui Na and the Psychosomatic Medicine Outpatient Department of the First Teaching Hospital of Tianjin University of Traditional Chinese Medicine, China. Seventy GAD patients will be randomly allocated to either the combined abdominal massage and medication group or the medication-only group. The study will involve various scale assessments, EEG examinations, and stool sample collections both pre- and post-intervention. Additionally, 35 healthy participants will be recruited to serve as normal controls and will undergo relevant tests and examinations upon enrollment. The trial flowchart is depicted in Figure 1, and the study timeline is outlined in Figure 2.

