Based on prior research, the Hamilton Anxiety Rating Scale (HAMA) score for the medication group was 18.61±3.17 [14]. The HAMA score for the treatment group is anticipated to decrease by 2.76 points. With a two-sided significance level (α) of 0.05 and a power of 90%, the required sample size was calculated using PASS 2021 software. This resulted in a needed sample size of N1=29 for the treatment group and N2=29 for the control group. Taking into account a potential dropout rate of 20%, a minimum of 35 subjects per group is needed, amounting to a total of at least 70 subjects. In addition, 35 healthy participants will be included in the study.

Intervention

Treatment Group GAD Patients

The medication regimen for this study will consist of oral escitalopram (Bailex) (Sichuan Kelun Pharmaceutical Co., Ltd., China; approval no.: National Drug Standard H20080788; specification: 10 mg × 10 tablets) [15]. Each participant will take 10 mg once daily at 09:00 AM for a duration of eight weeks.

In addition to the medication, participants in the treatment group will receive abdominal massages. The massage procedure will follow guidelines from the "Tui Na" textbook [16] edited by Fang Min and Wang Jingui (5th edition, "14th Five-Year Plan" for higher education in TCM). Participants will lie in a supine position while the practitioner performs rhythmic circular motions on the abdomen with the palm, 5 minutes clockwise and 5 minutes counterclockwise, at a frequency of 120 times/min. This is followed by finger massage on Zhongwan, Tianshu, Qihai, and Guanyuan points for 5 minutes at a frequency of 160 times/min. The total treatment time is approximately 15 minutes, conducted once daily, five days a week, for eight weeks.

To ensure the quality of the abdominal massage and the precise location of the acupoints, several measures will be implemented. Prior to the trial, [name] massage techniques, including force and frequency, will be calibrated using the YF-3 Hand Technique Measurement Instrument to create a standardized model. During the trial, experienced physicians with over 10 years of clinical practice will carry out the procedures. Additionally, all operators will receive training to ensure their techniques align with the model established by the YF-3 instrument.

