After GAD patients are enrolled, they will initially receive two weeks of abdominal massage treatment by a Tui Na doctor, followed by training in the technique. After two weeks, the force applied by patients during self-massage will be measured to standardize the technique. For the remaining six weeks, patients will visit the clinic once a week for treatment, with the remaining sessions performed at home. Patients will receive a video tutorial on abdominal massage and are required to upload videos and photos of their self-treatment for review. If inconsistencies are found, the doctor will provide online guidance. If the technique is corrected after three attempts, the patient will remain in the study; otherwise, they will be considered a dropout.

The acupoints utilized in this study are defined according to the 2021 national standard (GB/T12346-2021) titled "Names and Locations of Acupoints."[17] These acupoints include Zhongwan (CV12), which is situated in the upper abdomen, 4 cun above the navel along the anterior midline; Tianshu (ST25), located at the level of the navel, 2 cun lateral to the anterior midline; Qihai (RN6), found in the lower abdomen, 1.5 cun below the navel on the anterior midline; and Guanyuan (CV4), positioned 3 cun below the navel on the anterior midline. A map illustrating the locations of these acupoints is provided in Figure 3.

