**Figure 3 FIG3:**
[figure not shown]
Acupoint location diagram.

Control Group GAD Patients

Medication includes oral escitalopram (Bailex) (Sichuan Kelun Pharmaceutical Co., Ltd., China; approval no.: National Drug Standard H20080788; specification: 10 mg × 10 tablets), 10 mg once daily at 09:00 AM for eight weeks.

Healthy Participants

Healthy participants will not receive any treatment. They will be screened based on their medical history and HAMA scores. General information and HAMA scores will be recorded. Upon enrollment, EEG and stool samples will be collected from healthy participants.

Statistical analysis

This study will conduct statistical analysis based on the principle of intention-to-treat (ITT), including all patients who entered randomization and were not excluded in the statistical analysis. The efficacy endpoints will be analyzed using the full analysis set (FAS), supplemented by the per-protocol set (PP). Safety endpoints will be analyzed using the safety set (SS).

IBM SPSS Statistics for Windows, Version 26 (Released 2019; IBM Corp., Armonk, New York, United States) will be used for statistical processing. Measurement data will first be tested for normal distribution and homogeneity of variance. Data that meet the normal distribution and homogeneity of variance will be statistically described using the mean ± standard deviation (x̄±s), and data that do not meet the normal distribution and homogeneity of variance will be statistically described using the median (M) and the 25th and 75th percentiles (P_25_, P_75_).

For the comparison of measurement data between two groups, a paired two-sample t-test will be used for data that meet the normal distribution, and a rank-sum test will be used for data that do not meet the normal distribution. For the comparison of data at different time points after treatment with pre-treatment data, a paired t-test will be used for data that meet the normal distribution, and a rank-sum test will be used for data that do not meet the normal distribution. For the comparison of measurement data among multiple groups, a one-way ANOVA will be used for data that meet the normal distribution, and a rank-sum test will be used for data that do not meet the normal distribution.

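### Adverse events are recorded without an inquiry common to both arms, while the massage arm has 16 clinic sessions by design, so the between-arm safety comparison is at risk of ascertainment bias

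*Protocol article*

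**What the plan says.** **Safety text (Results, Safety assessments).** All participants have physical examinations and vital signs, and "Any adverse events will be documented in detail, and participants will receive appropriate treatment immediately". No timing or method of inquiry is given.

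**Massage arm (Intervention, Treatment Group GAD Patients).** Massage is "conducted once daily, five days a week, for eight weeks". After enrolment, "they will initially receive two weeks of abdominal massage treatment by a Tui Na doctor, followed by training in the technique". Then: "For the remaining six weeks, patients will visit the clinic once a week for treatment, with the remaining sessions performed at home". Patients also upload videos and photos of home sessions for review, and the doctor gives online guidance where the technique is inconsistent.

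**Medication-only arm (Intervention, Control Group GAD Patients).** The text gives the drug regimen, "10 mg once daily at 09:00 AM for eight weeks", and names no visit or contact.

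**Assessments (Study design and setting).** "The study will involve various scale assessments, EEG examinations, and stool sample collections both pre- and post-intervention". The schedule itself is in Figure 2, which is not shown.

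**Analysis (Statistical analysis).** Safety endpoints are analysed in the safety set. Count data are compared between groups with a χ² test at 0.05.

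**The concern.** Both arms take the same drug, and eligibility requires that no other anti-anxiety or psychiatric medication was taken in the month before. Drug-related events should therefore be about equally common in the two arms, apart from any effect of massage. Whether an event is recorded depends on someone learning of it, and the intervention gives massage patients many more occasions to mention one. If counts are compared as they arrive, a difference in contact can pass for a difference in safety. The probable direction is that massage looks worse on shared drug events and that such events are under-counted in controls.

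The Discussion deals with detection bias only through allocation concealment and assessors unaware of group. Neither changes how often a patient is seen. Safety is also part of the stated appeal of massage: the Introduction calls it safe, and the Discussion cites earlier work reporting no adverse effects.

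**Working it through.** The article gives no figure for safety contacts, so there is none to reproduce. The check has three steps.

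**1. Contacts that the text fixes for the massage arm**

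- All sessions: 5 per week × 8 weeks = 40.
- Weeks 1–2, delivered by a Tui Na doctor: 2 × 5 = 10. This applies the stated five days a week to the first two weeks and takes the sessions to be in clinic.
- Weeks 3–8, one clinic visit a week: 6 × 1 = 6.
- Clinic sessions: 10 + 6 = 16. Home sessions: 40 − 16 = 24, with uploads for review.

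**2. The two arms side by side**

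| Source of contact during treatment | Massage + drug | Drug only |
|---|---|---|
| Clinic sessions in the intervention text | 16 | none named |
| Review of uploads, online guidance | yes | none named |
| Assessments before and after treatment | yes | yes |
| Interim assessments in Figure 2 | not visible | not visible |
| Adverse-event inquiry common to both arms | none stated | none stated |

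The imbalance does not depend on what Figure 2 contains. Suppose controls were seen weekly (an assumption): that is 8 × 1 = 8 contacts, still against at least 16.

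**3. What unequal detection could do (illustration only)**

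The one input from the article is 35 patients per arm. True incidence p and the detection probabilities d are assumptions; the documents give neither. The recorded rate is p × d, with the same p in both arms and d = 0.9 under massage. The apparent risk ratio is 0.9 divided by the control detection. The last three columns give the chance of p < 0.05 in a two-sided comparison of proportions (normal approximation).

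| Control detection | Apparent risk ratio | p = 20% | p = 40% | p = 60% |
|---|---|---|---|---|
| 90% (equal) | 1.0 | 5% | 5% | 5% |
| 70% | 1.29 | 7% | 11% | 17% |
| 50% | 1.8 | 16% | 32% | 53% |
| 30% | 3.0 | 34% | 66% | 90% |

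For p = 40% and 50% control detection, the recorded rates are 0.4 × 0.9 = 0.36 and 0.4 × 0.5 = 0.20. That is 35 × 0.36 = 12.6 against 35 × 0.20 = 7.0 patients, a gap of 16 percentage points with no true difference. Exact enumeration over two binomials with an uncorrected χ² test gives 31.8% for this case, and 5.1% when both recorded rates are 0.36. The approximation is therefore adequate here.

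**The case against.** The strongest objection is that the control-arm side of the argument rests on silence. The document is a condensed article, Figure 2 is not shown, and the article mentions a clinical research manual and case report forms where adverse-event inquiry may be set out. The text also hints at more than two time points: Statistical analysis speaks of different time points after treatment and plans repeated-measures ANOVA, and the SCL-90 is described as used during treatment in patients generally. A reader might infer that controls have no contact between baseline and week 8, or that drug harms in controls will go unseen until then. The documents do not support either inference. The safety text covers all participants and any event.

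Three further objections stand:

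- The numerical illustration depends wholly on assumed incidence and detection. At 20% incidence and 70% control detection, the false-positive rate is only 7%.
- No comparative safety hypothesis is stated, and the χ² test is a general rule for count data. The primary outcome is not touched. A bias that makes massage look worse is conservative for a claim that massage is safe.
- The Introduction's remark that "Moreover, some patients may find the side effects of these medications intolerable and may opt to discontinue treatment" concerns pharmacotherapy for this disorder in general. It says nothing about how often this drug causes events in this trial.

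These points limit the concern but do not remove it. The additional massage-arm contacts belong to the intervention and remain whatever Figure 2 shows. An inquiry common to both arms is what would neutralise them, and the article states none.

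**Conclusion.** The point holds as a risk of bias. The article fixes 16 clinic sessions plus review of uploads for one arm, names no comparable contact for the other, and records adverse events without a common inquiry. Events from the shared drug may therefore be recorded more often in the massage arm, and an unadjusted comparison of counts may be biased, probably against massage.

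A reader might go further and say that the comparison is biased, or biased by a given amount such as 16 points. The documents do not support that, because they give no detection rates and do not show the full visit schedule. The size cannot be determined from them. The conclusion rests on two assumptions: that more contact means more events recorded, and that the unseen schedule does not already impose the same inquiry in both arms. It is worth correcting because the remedy is cheap, but it bears on the safety comparison only.

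**What to change.** Amend Safety assessments so that the same fixed, non-leading adverse-event questions are asked at the same calendar points in both arms, either at existing common assessments or by brief phone or message contact. State that the between-arm safety comparison uses those responses. Continue to record every other event, but list separately those volunteered at massage sessions and local massage effects such as abdominal soreness. If the full protocol already provides a common inquiry, one sentence saying so settles that part, and the basis of the comparison still has to be named.

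The cost is a short amendment and a few minutes of contact per patient for 70 patients. A channel for controls has to be set up, because the article describes uploads and online guidance for massage patients only. Controls would receive slightly more attention than now, and some events would move from the comparison to a separate listing.

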## Discussion

This study is a randomized controlled trial designed to investigate the therapeutic effects of abdominal massage (Tui Na) on GAD and explore the relationship between clinical efficacy and the gut MGBA.

The pathogenesis of GAD is complex and not fully understood, involving factors such as genetic predisposition, neurotransmitter changes, neuroendocrine dysfunction, immune system abnormalities, and disruptions in gut microbiota. With the advancement of gut microbiota research, the "gut microbiota-gut-brain axis" has emerged as a promising field in the study of mental and emotional disorders. This axis refers to the close connection between gut function and brain emotional cognition through neurotransmitter, endocrine, immune, and metabolic pathways, playing a crucial role in regulating behavior and emotions [20,21]. The brain can also regulate the structure and composition of gut microbiota to maintain intestinal microecological balance. The close relationship between gut microbiota and mental-emotional disorders has been increasingly confirmed by scientific experiments, which is significant for elucidating the pathogenesis of GAD and seeking new treatment methods.

In TCM, GAD can be categorized under the scope of "Yu Zheng" (depressive disorder), often caused by the blockage of Qi movement [22]. TCM recognizes the close relationship between the spleen, stomach, and emotions. The spleen and stomach are the pivot of Qi movement, and abdominal massage can directly regulate spleen and stomach functions, thereby adjusting the Qi movement, nourishing the heart, and calming the mind. The acupuncture points Zhongwan, Qihai, Guanyuan, and Tianshu, located on the abdomen, are crucial for strengthening the spleen and stomach and regulating Qi movement. Modern clinical research has also demonstrated that abdominal massage for GAD is comparable to Western medication in efficacy, with no adverse effects, and has significant advantages in alleviating accompanying symptoms such as bloating and loose stools [23,24]. Therefore, abdominal massage shows promise as an effective adjunctive therapy for treating GAD.

This study aims to design a high-quality randomized controlled trial to observe changes in brain electrical activity and clinical efficacy indicators before and after the combined treatment of abdominal massage and escitalopram in GAD patients. EEG recordings will be used to analyze the spontaneous and rhythmic electrical activity of brain cell groups, focusing on brain discharge indices and changes in alpha rhythms. Additionally, fecal 16S rDNA gene sequencing technology will be employed to examine the diversity, richness, and community structure of gut microbiota in GAD patients, as well as the regulatory effects of abdominal massage on these microbiota. This will help further elucidate the brain-gut interaction mechanism through which abdominal massage improves GAD based on the gut-brain axis theory.

However, this study has certain limitations in its design. Firstly, due to the nature of the intervention, it is impossible to blind the patients and the massage therapists. To minimize performance and detection biases, allocation concealment will be implemented, and outcome measurements will be conducted by assessors who are unaware of group assignments and interventions. Secondly, a fixed massage treatment protocol will be used for all participants in the trial without differentiation, which may not fully demonstrate the efficacy of the massage. Additionally, the sample size is relatively small. These potential limitations might affect the results and necessitate future studies.

